#### Blinding

2.4.2 

Participants or their legal representatives will be completely blinded to group allocation. Healthcare providers will only be aware of the feeding protocol used in their own center and will not be informed of group assignments in other centers. Outcome assessments will be conducted by a dedicated research team that is not involved in the implementation of the feeding protocols and is unaware of the grouping of these patients. For the primary outcome, after the study is completed, GI symptoms and daily feeding data recorded in the database will be reviewed and consolidated by the research team at the coordinating center to perform a unified evaluation. Statistical analyses will also be conducted by researchers at the coordinating center. Emergency unblinding will be permitted in cases of safety concerns or when significant differences in outcomes between groups are observed.

#### Interventional arms

2.4.3 

According to the randomization scheme, all centers will be assigned to either the intervention group or the control group in a 1:1 ratio before patient recruitment begins. Table 1 shows the schedule of enrollment, interventions, and assessments based on the SPIRIT 2013 statement (11). Detailed reporting checklists are provided in the Supplementary Table 1 (SPIRIT 2013 checklist) and Supplementary Table 2 (CONSORT–Cluster checklist) (12).

**TABLE 1 T1:** Schedule of enrollment, interventions, and assessments.

	Study period						
	Enrollment	Allocation	Post-allocation				Close-out
Timepoint	0–48 h	0–48 h	Day 1	Day 7	Day 28	Day 90	T_*E*_
Enrollment:							
Eligibility screen	X	–	–	–	–	–	–
Informed consent	X	–	–	–	–	–	–
Allocation	–	X	–	–	–	–	–
Interventions:	–	–	↔			–	–
(mNEED group)	–	–	↔			–	–
(Control group)	–	–	–	–	–	–	–
Assessments:	–	–	–	–	–	–	–
(Baseline characteristics)	X	X	–	–	–	–	–
(Muscle ultrasound assessment)	–	–	X	–	X	–	–
(Laboratory tests)	–	–	↔			–	–
(Therapies and medication use)	–	–	↔			–	–
(Critical illness and nutrition-related scores)	–	–	↔			–	–
(Nutrition delivery)	–	–	↔			–	–
(Gastrointestinal symptoms]	–	–	↔			–	–
(Rehabilitation therapy)	–	–	↔			–	–
(Clinical outcomes)	–	–	↔				–
(SF-36 and EQ-5D-5L)	–	–	–	–	X	X	
(Adverse events)	–	–	–	–	–	–	X

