This study also has important limitations. First, although FI was chosen as the primary outcome, its definition remains debated. Multiple diagnostic criteria exist; in this trial we adopted the widely accepted and relatively objective 2012 ESICM definition for FI, and applied the EFI definition as a prespecified sensitivity analysis. Despite this limitation, we consider FI the most suitable mediator between nutritional interventions and mortality. Second, center effects across nearly 100 ICUs are difficult to fully control. Although we stratified hospitals by level (secondary vs. tertiary) and performed randomization with a fixed seed, heterogeneity may still exist within the same level of hospitals—an inherent limitation of cluster-randomized designs, but also one that reflects the real-world variation in nutritional practice across China (19). Third, the feeding protocol in the control group was not entirely objective. Although based on the 2023 ESPEN guideline, interpretation of some aspects (e.g., initial feeding rate) remained subjective, which may have introduced variability in control group practices. Fourth, despite standardized ultrasound training delivered by CCUSG-certified instructors, operator-dependent variability could not be completely eliminated. Therefore, the change in muscle mass between day 1 and day 7 may be a more robust measure than the absolute value at day 7.

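### Table 1 schedules muscle ultrasound on Day 1 and Day 28 with a dash at Day 7, yet all four ultrasound secondary endpoints are defined on day 7

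*Protocol article*

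**What the plan says.** Three places in the protocol article fix the timing of the muscle scans.

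- **Section 2.4.3, Table 1.** The table has seven time columns: Enrollment, Allocation, Day 1, Day 7, Day 28, Day 90 and close-out. The row "Muscle ultrasound assessment" carries a mark at Day 1 and a mark at Day 28. Every other cell in the row, including Day 7, holds a dash.
- **Section 2.6.2, secondary outcomes.** Diaphragm thickness, quadriceps thickness, rectus femoris cross-sectional area and upper limb muscle thickness are each defined as a measurement on day 7, counted from ICU admission.
- **Section 3.1, limitations.** On operator variability, the authors write that "the change in muscle mass between day 1 and day 7 may be a more robust measure than the absolute value at day 7".

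The article describes no ultrasound outcome at day 28.

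**The concern.** A schedule of assessments should request every measurement that a listed endpoint needs. Here it requests two scans, and neither falls on the day on which the four muscle endpoints are defined. The Day 28 scan, in turn, serves no defined endpoint.

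The stake is data on four secondary outcomes. A day-7 scan that was not taken cannot be obtained later, and a day-28 value does not replace it: it is taken three weeks later, and only in patients who are alive and can be scanned then. If ICUs differ in which part of the article they follow, some will supply usable day-7 values and others none. The trial is spread over many sites (90 ICUs planned, 108 enrolled by 15 June 2025 according to section 2.4.1), so two readings of the same instruction are a practical possibility.

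**Working it through.** No sample-size or power formula applies. The check is whether the marks have been read against the right columns, and then whether any scheduled scan can supply an endpoint.

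**Step 1. Map the rows of Table 1 to its columns.** Each row below has seven cells for seven columns.

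| Row | Enrollment | Allocation | Day 1 | Day 7 | Day 28 | Day 90 | Close-out |
|---|---|---|---|---|---|---|---|
| Eligibility screen | X | – | – | – | – | – | – |
| Allocation | – | X | – | – | – | – | – |
| Muscle ultrasound | – | – | X | – | X | – | – |
| SF-36 and EQ-5D-5L | – | – | – | – | X | X | blank |

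**Step 2. Rule out a shifted column.** If the columns had slipped when the table was read from the PDF, other rows would disagree with the text as well. They do not.

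- The row "SF-36 and EQ-5D-5L" falls on Day 28 and Day 90, the two days that section 2.6.2 gives for both quality-of-life instruments.
- The interventions arrow starts at Day 1 and gives way to a dash at Day 90, so it ends at Day 28. That matches the 28-day intervention period in section 2.6.4.
- The clinical-outcomes arrow runs through Day 90, which matches 90-day mortality in section 2.6.2.
- Eligibility and allocation each fall in their own column.

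The ultrasound row has no empty cell, and its Day 7 cell holds an explicit dash.

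**Step 3. Compare endpoint days with scheduled days.**

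| Ultrasound endpoint (section 2.6.2) | Day defined | Scan scheduled that day in Table 1? |
|---|---|---|
| Diaphragm thickness | 7 | No |
| Quadriceps muscle thickness | 7 | No |
| Rectus femoris cross-sectional area | 7 | No |
| Upper limb muscle thickness | 7 | No |

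Ultrasound endpoints defined at day 7: 4 of 4. Scans scheduled at Day 7: 0. Ultrasound endpoints defined at day 28: 0. Scans scheduled at Day 28: 1.

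**Step 4. Size.** Section 2.6.2 lists 12 secondary outcomes: nutritional targets, 28-day mortality, 90-day mortality, SF-36, EQ-5D-5L, the four ultrasound measures, new infections, ICU length of stay and ventilator-free days. The share affected is 4/12, one third. The gap between the endpoint day and the second scheduled scan is 28 − 7 = 21 days.

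**Step 5. Which text is the outlier?** Sections 2.6.2 and 3.1 agree on day 7. Only the table differs, so it is the likelier place for the slip.

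**The case against.** The strongest reply is that this is one wrong cell. The four definitions agree with each other and with the limitations section. The full protocol (version 5.0, cited in section 2.1) is not shown. Section 2.4.3.3 says that every site receives ultrasound training before its first patient and has standardized measurement protocols and videos. Sites may well scan on day 7 whatever the article's table says. The table as read also has oddities: the control-group row is all dashes, and one quality-of-life cell is blank. A reading error is therefore unlikely but cannot be excluded altogether. All of this stands. It limits how much loss can be claimed, but it does not remove the contradiction.

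A reader might infer more than the article supports in four respects.

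- **That the four endpoints are lost.** Zero day-7 values is what a site following the table literally would produce. Nothing shows how many sites do so.
- **That mixed timing confounds the treatment comparison.** Both arms share one schedule and receive the same ultrasound training, and nothing suggests that timing errors differ by arm. Variation between ICUs means noise and missing data; bias between arms is not shown.
- **That the baseline-to-outcome interval varies because enrolment runs over 0–48 h.** Table 1 gives no origin for Day 1, so no range can be derived without an added assumption. The defined endpoints are day-7 values, and change from day 1 appears only as a remark in the limitations, so no defined endpoint depends on that interval.
- **That the multiplicity procedure is necessarily affected.** Section 2.7.1 applies false-discovery-rate control to clinical secondary endpoints without listing them. Whether the four muscle measures belong to that family is not stated.

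**Conclusion.** The contradiction is real: the schedule in Table 1 and the endpoint definitions in section 2.6.2 cannot both be followed as written. It touches all four ultrasound endpoints, 4 of the 12 listed secondary outcomes. It is more than cosmetic, because a site working from the table would collect nothing usable for them. The primary outcome and its sample size are untouched, and the endpoint definitions themselves are consistent, so moderate severity is appropriate.

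The conclusion rests on the table having been read correctly, which the alignment of the other rows supports. The actual loss of data depends on what sites have been told outside this article and cannot be estimated from it.

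**What to change.** Reconcile the ultrasound row of Table 1 with section 2.6.2:

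1. Mark the assessment at Day 7 as well as Day 1, and state in a footnote that Day 7 counts from ICU admission.
2. Say whether the Day 28 mark is an error or an additional exploratory scan. The article does not settle this, so the sponsor must.
3. Send all participating ICUs a short notice of the corrected timing.
4. Record the date of each scan, and let only day-7 scans enter the day-7 endpoints. Any tolerance around that day is for the analysis plan to set.

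The cost is a table correction and a site notice. Two scans per patient are already scheduled; a third would be needed only if the Day 28 scan is kept. The downside is that a few scans already taken on the wrong day could not be used for these endpoints. The correction is worth most while patients are still being recruited, because missed day-7 scans cannot be recovered.

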##### Arm#1 mNEED group

2.4.3.1 

If a center is randomized to the intervention group, training on the implementation of the mNEED nutrition protocol and ultrasound assessment will be conducted before enrolling the first patient. The mNEED protocol includes several modifications to the original NEED protocol:

For patients with AGI ≤ III, the risk of feeding intolerance (FI) is predicted using the NOFI model. Based on the predicted probabilities (< 30%, 30%–85%, and > 85%), different feeding strategies are adopted according to the threshold values identified from the NOFI decision curve analysis.The initial feeding rates have been reduced overall. Instead of the original rates of 25 mL/h for AGI < I and 15 mL/h for AGI II–III, the revised rates are: 20 mL/h for < 30% predicted FI risk, 15 mL/h for 30%–50%, and 10 mL/h for 50%–85%.For AGI ≤ III patients with a predicted FI probability > 85%, early EN (EEN) is deferred, and re-evaluation is performed after 12 h.The FI assessment interval has been extended from 4 to 6 h to every 12 h. Additionally, when the FIS (Feeding Intolerance Score) is 0, the incremental feeding volume has been reduced from 10 to 5 mL/h. The rationale for both adjustments is consistent with the overall strategy: to avoid overly rapid feeding advancement during the acute phase, which increases the risk of FI and early overfeeding.A new item has been added to limit energy provision to no more than 70% of the target caloric intake during the first 3 days, in accordance with ESPEN guidelines, to minimize the risk of early overfeeding.The decision to initiate supplemental parenteral nutrition (SPN) is based on evaluating the patient’s nutritional needs curve. The objective is to align nutritional delivery as closely as possible with this curve, ensuring adequate energy provision while avoiding overfeeding.

To monitor whether enrolled patients are managed in accordance with the study protocol, research staff at each participating center are required to complete a feeding record form for every patient until ICU discharge. This form includes detailed components of the FIS, with evaluations performed every 12 h. It records the FIS values and corresponding adjustments in the feeding rate. Upon study completion, electronic versions of the FIS record forms for all patients will be collected via email.

The detailed implementation flow of the mNEED protocol is presented in Figure 1. To facilitate the use of NOFI, we have developed a publicly accessible web tool for quick calculation of the predicted FI risk: https://[name].shinyapps.io/shiny_app/. In addition, a printable bedside nomogram was provided so clinicians can apply NOFI at the bedside when the web tool is unavailable.

**FIGURE 1 F1:**
[figure not shown]
Modified nutrition protocol for critically ill patients (mNEED) nutrition implementation process.

The management of GI adverse events follows the protocol established in the original NEED study (4). Each intervention center will receive a poster displaying the feeding protocol and GI event management flowchart, to be posted in the ICU ward for ease of reference and implementation.

##### Arm#2 Control group

2.4.3.2 

Centers randomized to the control group will follow general nutrition practices as recommended by the ESPEN guidelines. Prior to enrolling the first patient, training on the interpretation of the ESPEN guidelines and ultrasound assessment will also be provided. The control group does not follow a specified feeding protocol, but adheres to guideline-based principles, including: providing no more than 70% of estimated energy expenditure (EE) in the first 3 days; advancing to 80%–100% of EE by days 4–7; and initiating SPN on days 4–7 if EN alone is insufficient to meet nutritional needs.

Management of GI adverse events in the control group is consistent with that of the intervention group. Control group centers will also receive dedicated posters for reference and implementation.

##### Ultrasound training for both groups

2.4.3.3 

Ultrasound training will be provided to both intervention and control groups prior to the enrollment of the first patient at each center. All ultrasound training will be delivered by certified trainers from the Chinese Critical Care Ultrasound Study Group (CCUSG).

All participating centers involved in muscle ultrasound measurements are required to preserve each measurement as an ultrasound image. These images should be retained locally during the study and uploaded collectively after study completion. Standardized measurement protocols and instructional videos are available via the following platforms: Bilibili^3^ or YouTube^4^.

To address potential operator-dependent variability, we will account for it when reporting ultrasound outcomes, including inter-rater reliability metrics on a centrally read subset.

#### Protocol deviations

2.4.4 

##### mNEED group

2.4.4.1 

Major deviations [exclude from per-protocol set (PPS)]: Initial EN not delivered per protocol (speed or formula at start not matching protocol specification), or violation of the EN protocol more than once, as documented in the uploaded electronic feeding record.

Minor deviations (retain in PPS): Violation of the EN protocol no more than once.

##### Control group

2.4.4.2 

Major deviations: The EN speed reached 25 kcal/kg/day within 24 h of starting EN.

Minor deviations: Initial EN amount > 50% of 25 kcal/kg/day at start of EN.

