#### Secondary outcome definition and measures

2.6.2 

Achievement of nutritional targets: Receiving at least 80% of the estimated nutritional goals by day 7 after ICU admission(defined as energy intake ≥ 25 kcal/kg/day and protein intake ≥ 1.3 g/kg/day)28-day mortality: Assessed on day 28 after ICU admission90-day mortality: Assessed on day 90 after ICU admissionHealth-related quality of life (HRQoL) measured by SF-36 (Short Form-36 Health Survey): Assessed on days 28 and 90 after ICU admissionHealth-related quality of life measured by EQ-5D-5L (EuroQol 5 Dimensions 5 Levels): Assessed on days 28 and 90 after ICU admissionDiaphragm thickness: Measured on day 7 after ICU admissionQuadriceps muscle thickness: Measured on day 7 after ICU admissionRectus femoris cross-sectional area: Measured on day 7 after ICU admissionUpper limb muscle thickness: Measured on day 7 after ICU admissionNew infections in the ICU: Defined as infections newly acquired ≥ 48 hours after ICU admissionICU length of stayVentilator-free days: Ventilator-free days within 28 days in the ICU

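### The control-arm deviation limits do not match that arm's own 70% feeding ceiling, so deviation reporting and the per-protocol set rest on a different standard from the feeding rule

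*Protocol article*

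**What the plan says.** **Control feeding rule (section 2.4.3.2).** "The control group does not follow a specified feeding protocol, but adheres to guideline-based principles". Among those principles is a numeric ceiling, "providing no more than 70% of estimated energy expenditure (EE) in the first 3 days", followed by "advancing to 80%–100% of EE by days 4–7". Supplemental parenteral nutrition may be started on days 4–7 if enteral nutrition (EN) falls short.

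**Adherence check (section 2.6.3).** Daily energy and protein intake in controls is a process measure. Its stated purpose is to see whether feeding followed the guideline pattern, and the 70% ceiling for 3 days is given as the example.

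**Control deviation limits (section 2.4.4.2).** There are two grades: "Major deviations: The EN speed reached 25 kcal/kg/day within 24 h of starting EN" and "Minor deviations: Initial EN amount > 50% of 25 kcal/kg/day at start of EN". Neither refers to 70%, to EE, or to any time beyond the first 24 h of EN.

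**mNEED deviation limits (section 2.4.4.1).** A major deviation excludes the patient from the per-protocol set (PPS). It is a wrong start "or violation of the EN protocol more than once, as documented in the uploaded electronic feeding record". A single violation is minor and the patient is retained. Section 2.4.3.1 lists a 70% limit for the first 3 days, set against target calories, as part of the mNEED protocol.

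**Use of the PPS (section 2.7.1).** The PPS serves sensitivity analyses. It is defined there as patients with at least 48 h of protocolized EN.

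**The concern.** A deviation rule should flag patients who depart from what their arm was told to do. In the control arm the instruction and the flag use different quantities (energy provided against EN rate or starting amount), different references (estimated EE against a fixed 25 kcal/kg/day), different periods (3 days against the start or first 24 h of EN) and different levels (70% against 100% or 50%). The rule can therefore pass a patient fed well above the ceiling and flag one fed within it.

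The arms are also held to different standards on a limit they share. If the 70% limit counts as part of the mNEED EN protocol, breaching it more than once there is major and removes the patient from the PPS. The same pattern in a control may not be graded at all. At stake are the deviation tables and the make-up of the PPS, which is meant to support the primary result.

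**Working it through.** The plan gives no figure for this comparison, so there is none to reproduce. The check sets the limits on one scale.

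**Inputs.** Ceiling: 70% of EE, days 1–3 (section 2.4.3.2). Major limit: 25 kcal/kg/day within 24 h of EN start. Minor limit: more than 50% of 25 at the start (both section 2.4.4.2). EE is not stated. 25 kcal/kg/day is assumed as the base case, because section 2.4.4.2 uses it as the reference and section 2.6.2 describes the nutritional goal as "defined as energy intake ≥ 25 kcal/kg/day and protein intake ≥ 1.3 g/kg/day". A range of EE is shown below.

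**Limits at EE 25.**
- Ceiling: 0.70 × 25 = 17.5 kcal/kg/day.
- Minor limit: 0.50 × 25 = 12.5 kcal/kg/day.
- Major limit against ceiling: 25 / 17.5 = 1.43, so 43% above it.

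**Range of EE.** The ungraded band in the first 24 h runs from 0.70 × EE to just under 25.

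| EE | Ceiling | Width of band |
|---|---|---|
| 20 | 14.0 | 11.0 |
| 25 | 17.5 | 7.5 |
| 30 | 21.0 | 4.0 |
| 35.7 | 25.0 | 0 |

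The band closes at EE = 25 / 0.70 = 35.7.

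**Over the ceiling, not flagged (EE 25, EN the only energy source, EN starting on day 1).** The patient starts at 12.5, which is not above the minor limit, rises to 24.9 at hour 12, which is not at the major limit, and stays there.
- Day 1: (12.5 × 12 + 24.9 × 12) / 24 = 18.7 kcal/kg, or 18.7 / 25 = 75% of EE.
- Days 2 and 3: 24.9 each.
- 3-day mean: (18.7 + 24.9 + 24.9) / 3 = 22.8 kcal/kg/day, or 22.8 / 25 = 91% of EE.

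All three days exceed 70%, and neither grade applies. Reaching 25 or more only after the first 24 h of EN is also ungraded, because no control limit looks past that point.

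**Within the ceiling, flagged (EE 25).** A start at 15 kcal/kg/day, held, is 15 / 25 = 60% of EE. It complies with the ceiling and is logged as minor. The same holds for any start above 12.5 and up to 17.5.

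**Rate against energy.** A high rate reached late on day 1 need not breach that day's ceiling. At 12 until hour 20 and then 24, intake is (12 × 20 + 24 × 4) / 24 = 14 kcal/kg, or 56% of EE. The breach comes from an earlier rise or from holding the rate on later days.

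**The case against.** The strongest reply is that a care principle and a deviation grade are different things. The control arm has no stepwise protocol, section 3.1 concedes that parts of it, such as the initial rate, are open to interpretation, and a tolerant threshold for major deviations may be deliberate. It is also reasonable that an arm with a stepwise protocol is judged by its steps. This stands as far as it goes: a graded threshold is legitimate. It does not explain why the minor tier is stricter than the ceiling at the start of EN and absent afterwards, so that sustained over-ceiling feeding can fall in neither grade. Nor does it explain why the deviation limits use another reference from the adherence check in section 2.6.3.

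A second reply is that true adherence will be visible anyway, because section 2.6.3 reports control intake against the 70% pattern. That is correct, and it limits the harm.

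A third concerns timing. Section 2.4.4.2 counts from EN start. If the first 3 days are ICU days and EN starts on day 2, the 24-h window falls on days 2–3. It would therefore be wrong to say that intake on days 2–3 can never be a major deviation. What holds is that nothing after the first 24 h of EN is graded.

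A reader might also count it as a gap that a control held at low EN through day 7 is not graded. The documents do not support that. The rule concerns energy provided and allows parenteral supplementation, so low EN alone does not break it.

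**Conclusion.** The point holds in a limited form. As written, section 2.4.4.2 does not measure departure from the ceiling in sections 2.4.3.2 and 2.6.3. At an assumed EE of 25 kcal/kg/day, the major limit lies 43% above the ceiling, a 3-day mean of 91% of EE can pass with no deviation, and starts above 12.5 and up to 17.5 are logged although allowed. The early gap does not hinge on that assumption; it exists for any EE below 35.7.

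The effect is confined to deviation reporting and the PPS sensitivity analysis. Even the PPS effect is partly inferred: the exclude and retain labels appear only under the mNEED arm and are read across to controls, and the 48-h definition in section 2.7.1 does not by itself remove over-ceiling controls.

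A reader might infer that a lower rate of feeding intolerance (FI) under mNEED could come from overfed controls whom the trial reports as adherent. The documents do not support this. The wording of a deviation grade does not change how controls are fed, the primary analysis is by intention to treat on the full analysis set, and the process measures would show the excess. The direction of any bias in the PPS is also uncertain. Section 2.4.3.1 links rapid advancement to more FI, but section 2.6.1 also counts failure to reach 20 kcal/kg/day enterally within 72 h as FI. At EE 25 that is 80% of EE, above the ceiling, so over-ceiling feeding could lower FI on that component.

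**What to change.** Reconcile sections 2.4.3.2, 2.4.4.2 and 2.6.3 so that the upper limit for a control deviation and the control feeding rule use the same ceiling, the same days, the same clock (ICU admission or EN start) and the same reference (estimated EE or 25 kcal/kg/day). Which limit is clinically right is for the investigators; no view is taken here. State the exclude and retain consequences for controls explicitly, and align them with the PPS definition in section 2.7.1.

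Derive the grade by program from the daily intake already collected, including for patients already enrolled, before allocation is joined to outcomes.

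Do not make failure to advance on days 4–7 a ground for PPS exclusion. Low enteral delivery is a component of the primary outcome, so such a rule would remove control FI cases from the PPS because of their outcome.

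The cost is a short revision of wording and one programmed derivation. If the deviation limit is brought to the ceiling, more controls are likely to be recorded as deviating and the control PPS to be smaller.
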